# Study protocol for the family empowerment program: a randomized waitlist-controlled trial to evaluate the effectiveness of online Community Reinforcement and Family Training (CRAFT) on the wellbeing of family members with a relative experiencing substance dependence and mental illness

**DOI:** 10.1186/s12888-023-05487-0

**Published:** 2024-01-10

**Keywords:** Rural, Substance disorder, Online therapy, Community reinforcement and family training, Family, Mental health

## Abstract

**Background:**

Systematic reviews consistently show that family-focused interventions are effective at improving substance treatment engagement and outcomes across the lifespan. Yet, Australian substance use treatment services rarely incorporate family members and concerned significant others. Testing of family focussed interventions in the Australian context is required.

**Methods:**

The trial is a randomized wait-list control trial assessing the effectiveness, feasibility and acceptability of online CRAFT with a parallel group. Participants will be randomised to receive either online CRAFT or to a wait-list control group who are provided with CRAFT related reading material during the waiting period. Outcomes will be assessed at baseline and then at 6- and 15-weeks post baseline. The primary outcome will be improved wellbeing of participating family members. The trial reporting will comply with SPIRIT guidelines.

**Discussion:**

This study will focus on people living in rural areas. Substance treatment programs are limited in rural Australia. The provision of the Family Empowerment Program (CRAFT) online should make family focused substance treatment support accessible and attainable for the first time in rural areas. The outcomes of this trial could have meaningful implications for the future funding and support of family focused substance treatment services that are inclusive of people with mental health conditions.

**Trial registration:**

ANZCTR, ACTRN12623000796684p, Registered 26 July 2023. Prospectively registered with protocol version 3.

**Supplementary Information:**

The online version contains supplementary material available at 10.1186/s12888-023-05487-0.

## Background

Substance use is associated with poor outcomes for individuals with mental illness because it impedes treatment engagement and is associated with more severe psychiatric symptoms [1]. Systematic reviews consistently show that family-focused interventions are effective at improving substance treatment engagement and outcomes across the lifespan [2, 3]. Yet, substance treatment services rarely incorporate family members and concerned significant others [4]. Integrated treatment, care and support for people living with mental illness and substance use is the goal of policy and practice in Australia and internationally. However, while the direction has been given by state and national governments to “do” integrated care, there are no frameworks or guidelines about what to do [5]. Ways to address problematic substance use of people with a mental illness are needed and family members are best placed to provide support.

According to the Australian Institute of Health and Welfare [AIHW], 45% of all Australians aged 16 to 85 years — 8.7 million people — will experience mental illness at some point in their life [6]. The most common conditions are anxiety, depression and alcohol dependence. Mental illness and substance misuse are the second largest contributor (23%) of the non-fatal burden of disease in Australia with $9.9 billion being spent on mental health in 2017–18 [7]. Given the prevalence and social and economic costs of mental illness including substance dependence, access and effectiveness of mental health services is crucial.

Harmful substance use and related deaths are more prevalent in rural Australia compared to cities [8]. However, substance treatment services are mostly located in large cities rather than in regional or rural areas [9]. Further, services can meet only one third of the demand for treatment [9]. Few of these services provide support to family members. Only 7% of the 139,300 clients receiving treatment in 2021 were family or friends of people with a substance problem [9].

In Australia, one in three individuals with a substance use disorder also has a mental health disorder [6]. Two or more conditions are so common among those experiencing mental health or substance use problems that “comorbidity is seen as the rule rather than the exception” [10]. Further, comorbidity results in a greater care burden on the family and increased family conflict compared to single disorders [11–13]. However, very often the presence of co-occurring conditions excludes people from participating in clinical trials and the efficacy of interventions for people with more than one condition is unknown [14].

The aim of the current study is to implement and evaluate Community Reinforcement and Family Training (CRAFT) delivered online by trained counsellors to people living in rural Australia. CRAFT is an evidence-based approach that helps families to reduce a relative’s substance use, engage in treatment, and improve family wellbeing through structured, personalised training and support [2, 15–17]). However, CRAFT is not available in Australia and has limited evidence for mental illness and substance use combined [12]. Derived from Cognitive Behavioural Therapy (CBT) and Motivational Interviewing (MI), the aims of CRAFT are to teach family members how to remove positive reinforcement for problematic substance use behaviour effectively and safely, increase positive reinforcement for non-using behaviour, and help the person with problematic substance use to enter, or be retained in, treatment [18]. In addition, CRAFT aims to improve family members’ social and emotional wellbeing.

In this iteration, CRAFT will be delivered as The Family Empowerment Program, emphasizing family members as the primary target group for the study and aiming to establish CRAFT as a family-focused therapy program in Australia. The study will generate the first Australian outcome data, which will complement the USA outcome data [12] and the Australian adaptation and acceptability data from the team’s previous work [16, 19]. This research project can inform future health system policy on the provision of virtual care for rural Australian families of people with substance dependence and mental illness.

### Objectives of the study

This trial will determine the effectiveness of an online delivered CRAFT counselling intervention for improving the well-being of family members with a loved one experiencing substance problems with and without co-occurring mental health problems. It is hypothesised that CRAFT implemented online by accredited therapists will be more beneficial than CRAFT self-help information provided to the wait-list group. Compared to the wait-list control group, the CRAFT group will show significant decrease in self-reported levels of depression, anxiety and stress and significant increase in life satisfaction and that these improvements will be maintained over a three-month period post intervention.

It is hypothesized that 1) improvements in depression, anxiety and stress scores as a function of CRAFT relative to the control group will be mediated by: a) acceptability of receiving support online and b) ease of access. Given the lack of information regarding implementation parameters of substance use interventions for families of people with a mental health condition, qualitative methods will explore the experiences of study participants as well as clinicians delivering the program. The study has the following specific aims:

Aim 1: determine the effectiveness of an online delivered CRAFT counselling intervention on on self-reported levels of depression, anxiety, stress and life satisfactionAim 2: qualitatively examine the paricipants’ experiences about the acceptability of receiving support onlineAim 3: qualitatively examine the clinicians’ experiences of delivering the program and feasibility

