## Methods

### Study design

This is a randomized wait-list control trial that will evaluate the effectiveness, feasibility and acceptability of online CRAFT with a parallel group. Participants will be randomised to receive either online CRAFT for 6 sessions over 6 to 10 weeks or to a wait-list control group who are provided with CRAFT related reading materials during the waiting period. Outcomes will be assessed at baseline and then at 6- and 15-weeks post baseline. Outcome measures will be completed online independently of researchers or clinicians. The trial reporting will comply with CONSORT guidelines. Figure 1 provides an overview of the trial recruitment and process.

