### Randomisation and blinding

The randomisation procedure for this project will be conducted by an independent researcher ([name]) using STATA software (Version 18 MP) and with the 'randomizr' package. This researcher will not be involved in other aspects of project implementation, such as CRAFT delivery or data collection. The researcher (NS) who recruits the participants will have no access to the order of allocation. All participants will be allocated an identification number and, before completing their baseline measures, will be randomly allocated to either the CRAFT group or the wait list control group. Individuals randomized to the control group will be assigned a 6-week wait time.

All assessments are conducted online, thus minimizing the possibility of researcher bias. Analysis of results will be blinded to the clinicians delivering CRAFT. The clinicians will be provided with contact information of consenting participants and they will deliver the program as scheduled without knowing which group the person is allocated to. Trial participants will be informed their start date for the intervention as 1. as soon as possible (Group A—within 7 days) or 2. within 6 weeks (Group B—WLC) without being informed which group they are in. The need for unblinding is not anticipated.

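### The schedule cannot show a benefit over wait-list maintained for three months: week 15 falls 4–9 weeks after CRAFT ends, and by then controls have also been offered CRAFT

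*Protocol article*

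**What the plan says.** All references are to the protocol article.

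- **Hypothesis (Objectives of the study).** "Compared to the wait-list control group, the CRAFT group will show significant decrease in self-reported levels of depression, anxiety and stress", with a rise in life satisfaction. The same sentence continues that "these improvements will be maintained over a three-month period post intervention".
- **Intervention (Study design).** Participants in the CRAFT arm receive "online CRAFT for 6 sessions over 6 to 10 weeks".
- **Comparator (Study design).** The other arm is a "wait-list control group who are provided with CRAFT related reading materials during the waiting period".
- **Visits (Study design).** "Outcomes will be assessed at baseline and then at 6- and 15-weeks post baseline". Table 1 gives the same three time points for the DASS-21 and the Satisfaction with Life Scale and lists no later one.
- **Start of treatment (Randomisation and blinding).** "Individuals randomized to the control group will be assigned a 6-week wait time". The same section says participants are given a start date of either "as soon as possible (Group A—within 7 days") or "within 6 weeks (Group B—WLC").
- **Analysis (Statistical analysis).** Mixed-effects regression is planned for the primary outcomes, with adjusted effects reported by intention to treat. The section names no time point for the main contrast.

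**The concern.** The sentence in the objectives makes two commitments: a comparator (the wait-list group) and a duration (three months from the end of the intervention). The visit schedule and the wait time appear to meet neither. The last visit comes too soon after the programme ends, and the control arm has by then been offered the same programme.

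The results could be misread in two ways. If CRAFT works in both arms, the between-arm difference at week 15 should shrink, and that could be reported as a failure to maintain benefit. Conversely, stable scores in the CRAFT arm at week 15 could be reported as three-month maintenance over control, when the interval is shorter and no untreated group remains. The Discussion expects the results to bear on funding of family services, so either error would have consequences.

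**Working it through.** **Inputs.** CRAFT arm start: 0 to 1 week. Course length: 6 to 10 weeks. Control wait: 6 weeks. Last assessment: week 15. Assumptions: three months is about 13 weeks, and the start windows run from a date close to baseline.

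**1. Time from end of CRAFT to the last visit.** Gap = 15 − (start + course length).

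| Start (week) | Course (weeks) | Ends (week) | Gap to week 15 | Visit needed for three months |
|---|---|---|---|---|
| 0 | 6 | 6 | 9 weeks | week 19 |
| 0 | 10 | 10 | 5 weeks | week 23 |
| 1 | 6 | 7 | 8 weeks | week 20 |
| 1 | 10 | 11 | 4 weeks | week 24 |

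The stated three months is not reproduced under any schedule. The gap is 4–9 weeks (0.9–2.1 months), so the shortfall is 13 − 9 = 4 weeks at best and 13 − 4 = 9 weeks at worst.

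**2. What controls have received by week 15.** With a start at week 6, a 6-week course ends at week 12 and a 10-week course at week 16. Controls have 15 − 6 = 9 weeks of access. Any course of 9 weeks or less is complete. At an even pace, a 10-week course has delivered 6 × 9/10 = 5.4 of its 6 sessions. Week 15 therefore compares arms that have both had all or nearly all of CRAFT, one earlier than the other.

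**3. What week 6 can show.** If the full 6-week wait is observed, week 6 is the only follow-up visit at which controls have had reading material alone. In the CRAFT arm, only a participant who starts at once and finishes in 6 weeks has completed the course by then. The two descriptions of the wait matter here: a fixed 6 weeks keeps controls untreated until week 6, while a start at any time up to 6 weeks does not guarantee it.

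**4. Illustration of pooling the two follow-ups.** The plan does not say that it will pool. Assumptions, none of them in the documents: effect 0.40 SD at week 6 and 0 at week 15, so 0.20 SD on average; correlation 0.6 between all visits; two-sided 5% test. Per arm, n = 260 × 0.8 / 2 = 104. Power = Φ(effect/SE − 1.96).

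- Unadjusted, week 6: SE = √(2/104) = 0.139; 0.40/0.139 = 2.88; power about 82%.
- Unadjusted, average of both visits: SE = √(2/104 × (1 + 0.6)/2) = 0.124; 0.20/0.124 = 1.61; power about 36% (38% to 35% for correlations 0.5 to 0.7).
- Baseline-adjusted, week 6: SE = √(2/104 × (1 − 0.36)) = 0.111; power about 95%.
- Baseline-adjusted, average: SE = √(2/104 × (0.80 − 0.36)) = 0.092; power about 58%.
- If 0.20 SD remained at week 15, the average effect would be 0.30 SD and unadjusted power about 68%.

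**The case against.** The strongest reply is that the hypothesis has two steps: a between-arm improvement, then durability within the CRAFT arm. On that reading week 15 does provide data. This stands in part. Within-arm change to week 15 is measured and can be described, so a reader who inferred that nothing can be learned about durability would go too far. But the sentence opens with the wait-list comparison, and the improvements it refers back to are that comparison's. Even on the within-arm reading, the three-month duration fails.

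A second reply is that treating controls after the wait is inherent in a wait-list design and is openly stated. That is right: the crossover is no fault in itself. The fault is an objective that claims more than the crossover leaves room for.

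A third is that the choice of time point and the group-by-time terms commonly belong in a statistical analysis plan or full protocol, neither of which is shown. That also stands. A reader might infer from the analysis section that one effect will be pooled over weeks 6 and 15, or that maintenance will be judged by a between-arm test at week 15. The article says neither, so the power loss above is not a property of the plan. No analysis plan, however, can add a later visit or an untreated group at week 15.

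Finally, a reader might conclude that week 6 is the only randomised comparison. It is not. Week 15 still compares the groups as randomised, but it answers a different question: early against delayed CRAFT.

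**Conclusion.** The objective is wrong as written. Its duration conflicts with the article's own schedule: 4–9 weeks of follow-up after the programme, against about 13 weeks stated. Its comparator is no longer untreated at the last visit, because controls begin CRAFT at or by week 6. A small difference at week 15 would not show loss of benefit, and a stable CRAFT arm would not show maintenance relative to control.

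The timing result rests only on the stated start windows, course length and visit weeks, and on baseline being close to the date from which the start windows run. If every CRAFT participant started exactly at baseline, the gap would be 5–9 weeks, which changes nothing. The power figures (about 82% to 36% unadjusted, about 95% to 58% with baseline adjustment) rest on assumed effects, an assumed correlation and an estimator the plan does not specify. They show only why pooling should be avoided, and the conclusion does not depend on them.

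The week-6 hypothesis is not undermined, provided controls have not started CRAFT before that assessment. It is in large part an on-treatment comparison.

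**What to change.** 1. In the objectives, replace the three-month wording with: 15 weeks after baseline (about 4–9 weeks after programme end).
2. Name the group-by-time contrast at week 6 as the primary CRAFT-versus-wait-list effect. State that participants on schedules longer than 6 weeks are still in the programme at that point.
3. Report week 15 as uncontrolled within-arm change in the CRAFT arm, plus a randomised comparison labelled early versus delayed CRAFT. Draw no inference about maintenance relative to an untreated control, and do not pool weeks 6 and 15 into one treatment effect.
4. Reconcile the two statements of the control wait in the randomisation section, since the meaning of the week-6 contrast depends on which applies.

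These changes are to wording in the objectives, the randomisation section and the analysis section, and should be made before any comparative analysis. They need no new visit and no change to the sample size. The cost is a weaker maintenance claim. Adding a later visit would not by itself rescue the stronger one: a visit at weeks 19–24 would supply the three months but still have no untreated comparator.

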### Recruitment and follow-up procedures

Participants will be recruited from any rural areas in Australia by advertisements through healthcare and substance treatment agencies and health advice internet sites, in local newspapers and radio stations and paid geo-located (rural) social media advertisements (see Supplementary Material). The advertisement will include information about CRAFT, highlighting that the program’s goals are to improve the participants’ mental health and increase the likelihood of their relative’s engagement in treatment. Individuals who are interested in participating will register on a secure website or by contacting the study coordinator.

Those who are registered will be contacted within 48 h and invited to complete a short telephone screen using the inclusion and exclusion criteria. If eligible, the study information and process will be described, and verbal consent will be gained. Following this, participants are randomised to either the waitlist or intervention group, and a first initial appointment is organised with an in-community CRAFT practitioner. Participants will then be sent a link to the written consent form and outcome measures.

On average, the information and screening process will take approximately 20–30 min to complete. Once the consent is signed, the participant can access the online baseline measures for completion. If the measures are not completed, SMS reminders will be sent after 2 days. If the participant still does not complete the measures, they will be contacted by phone to confirm their intent to join the study and to ensure that they can access the survey. Participants who complete all three surveys (baseline, 6 and 15 weeks) will receive $120AUD in gift card for their time and participation. Individuals who have not responded to the initial call or have not completed the follow-up measures will be contacted on a weekly basis by both phone and SMS for up to 4 weeks after the follow-up is due.

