#### Statistical analysis

This study will employ a three-stage analytical approach. In the first stage, baseline characteristics of study participants will be identified using descriptive statistics and standard deviations [30]. The second stage involves bivariable analysis using the chi-square test for categorical variables and the t-test for continuous variables, including the estimation of differences in proportion and mean (difference-in-difference) between intervention groups [30]. To assess the intervention's effects on primary outcomes, mixed effect regression modelling will be applied. Intervention effects will be quantified using mean differences (MD) for continuous variables and relative risks (RR) for categorical variables, along with their corresponding 95% confidence intervals (CI) [31]. The primary results will be based on adjusted effect measures, and all analyses will adhere to the intention-to-treat (ITT) principle [32]. STATA version 18 will be used for the analyses, and statistical significance will be declared by *p*-values < 0.05.

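### The hypothesis of benefit over wait-list maintained for three months after the intervention cannot be tested: the last assessment falls 4 to 9 weeks after the course, when controls are due most or all of their own CRAFT

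*Protocol article*

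**What the plan says.** The hypothesis is comparative. In the protocol article, Objectives of the study: "Compared to the wait-list control group, the CRAFT group will show significant decrease in self-reported levels of depression, anxiety and stress". The same sentence adds a gain in life satisfaction and then says that "these improvements will be maintained over a three-month period post intervention".

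The timing is set elsewhere in the article:

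- Study design, treatment: "Participants will be randomised to receive either online CRAFT for 6 sessions over 6 to 10 weeks or to a wait-list control group".
- Study design, assessments: "Outcomes will be assessed at baseline and then at 6- and 15-weeks post baseline". Table 1 agrees and has no later column.
- Randomisation and blinding, immediate group: the start is given as "as soon as possible (Group A—within 7 days".
- Randomisation and blinding, controls: "Individuals randomized to the control group will be assigned a 6-week wait time". The same section says that participants in this group are told they will start inside six weeks, and that allocation comes before the baseline measures are completed.
- Recruitment and follow-up procedures: overdue surveys are pursued by phone and SMS "for up to 4 weeks after the follow-up is due".
- Statistical analysis: mixed-effect regression for the primary outcomes, and "all analyses will adhere to the intention-to-treat (ITT) principle".

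**The concern.** The hypothesis makes two demands of the design: an assessment about three months after treatment, and a comparison group that is still untreated then. The published schedule appears to supply neither.

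What is at stake is how week 15 is interpreted. A favourable result could be taken as three-month durability when the follow-up is roughly one to two months. A null difference between arms could be taken as fading benefit when the controls have simply caught up on treatment. The Discussion expects the results to bear on service funding, so the distinction matters.

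**Working it through.** **Inputs.** Course length 6 to 10 weeks and assessments at weeks 6 and 15 (Study design). Start 0 to 1 week for the immediate group and a 6-week wait for controls (Randomisation and blinding). Reminders for up to 4 weeks (Recruitment and follow-up procedures). Three months = 365.25 / 4 / 7 = 13.0 weeks. I assume that start times are counted from baseline; the article does not say so.

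**Step 1: follow-up after the course.** Course end = start + length. Gap = 15 − course end. A true three-month assessment is due at course end + 13.

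| Start (week) | Length (weeks) | Course ends (week) | Gap at week 15 | Short of 13 by | Three-month date (week) |
|---|---|---|---|---|---|
| 0 | 6 | 6 | 9 | 4 | 19 |
| 1 | 6 | 7 | 8 | 5 | 20 |
| 0 | 10 | 10 | 5 | 8 | 23 |
| 1 | 10 | 11 | 4 | 9 | 24 |

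The stated three months is not reproduced by any combination. Counting from the last of six weekly sessions (start + 5, so week 5 to 6) gives 15 − 6 = 9 to 15 − 5 = 10 weeks, still short.

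**Step 2: could late surveys close the gap?** The latest pursued response is at week 15 + 4 = 19. That is 19 − 11 = 8 to 19 − 6 = 13 weeks after the course, or 13 to 14 weeks after a last weekly session. Counted from the end of the course, only the latest responders with the fastest courses reach three months, and those are overdue surveys.

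**Step 3: could a loose anchor close it?** For week 15 to fall 13 weeks after the course, the start would have to be at 15 − 13 − length: −4 weeks for a 6-week course and −8 for a 10-week course. Counting from a last weekly session it is 15 − 13 − 5 = −3. The first session would have to precede baseline by 3 to 8 weeks. Reminders for an incomplete baseline go out after 2 days and are followed by a phone call, so the article does not describe a gap of that size.

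**Step 4: controls at week 15.** They are 15 − 6 = 9 weeks past their due start. A 6-week course would end at week 12 and a 10-week course at week 16. With evenly spread sessions, that is 6 of 6 for the shorter courses and 5 to 6 for a 10-week course.

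**Step 5: the week-6 survey.** In the immediate group the course ends at week 6 to 11, so some participants may still be in treatment; the share is unknown and could be zero. In the control group the position depends on the clock. A 6-week wait counted from randomisation ends before a survey due 6 weeks after baseline, by however long baseline completion took. The wording told to participants also permits an earlier start. A control starting at week 6 who answers at the end of the reminder period (6 + 4 = week 10) would have had 4 weeks of CRAFT. At one session per sixth of the course, that is 5 sessions (6-week course), 4 (8-week) or 3 (10-week). How many would answer that late is unknown.

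**The case against.** The strongest reply is that crossover is an open and familiar feature of a wait-list design. On this view *maintained* naturally means within the CRAFT arm: the gain is first shown against controls and then followed. On that reading the crossover half of the point falls away. The shortfall in follow-up does not. The three-month phrase also appears only once, and no calculation depends on it. That limits the weight of the point without making the sentence testable. The trial flow figure is not shown and may clarify wait-list timing, but the text and Table 1 agree on the assessment times.

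Four stronger readings are tempting and are not supported:

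- *Week 6 is a clean comparison with untreated controls.* The article does not guarantee this. It states both a 6-week wait and a start inside six weeks, and randomisation and booking of the first appointment precede baseline.
- *The article is at fault for not naming the primary time point.* A condensed article may leave that to the full protocol or analysis plan.
- *The week-15 comparison, or the trial, is invalid.* Immediate against delayed CRAFT is still a valid randomised comparison; it answers a different question. The week-6 intention-to-treat contrast also stands as CRAFT offered now against reading material and a wait.
- *A later survey is required.* A survey at week 24 would fall 24 − 11 = 13 to 24 − 6 = 18 weeks after the course, so it would match three months only for the slowest courses, and it would still lack an untreated comparison.

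**Conclusion.** The concern holds. The last scheduled assessment is 4 to 9 weeks after the course, which is 4 to 9 weeks short of three months (3 to 4 weeks short if counted from a last weekly session). By then controls are due 5 to 6 of 6 sessions. No analysis can supply the missing follow-up or the missing untreated group, so this is not detail that an analysis plan could settle.

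The result assumes that start times run from baseline and that courses keep to the stated length. Ordinary slippage of some days does not change it. If control waits run from randomisation, controls have had more exposure by week 15, which strengthens the second half.

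This should be corrected, but it does not undermine the trial. Week 6 is the right place for the CRAFT-versus-wait-list conclusion, provided that control start dates are tied to it. It should be read as the effect of offering CRAFT, not of a completed six-session course.

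**What to change.** 1. **Objectives of the study.** Replace the three-month clause with: *Within the CRAFT arm, outcomes will be described at week 15, about 4 to 10 weeks after treatment, without an untreated comparison.*
2. **Statistical analysis.** Add: *The conclusion on CRAFT versus wait-list will be drawn from the week-6 intention-to-treat contrast; any difference between arms at week 15 will be labelled immediate versus delayed CRAFT.*
3. **Randomisation and blinding.** State one rule for controls: session 1 is booked after the due date of the week-6 survey, counted from baseline. Align what participants are told about their start with this rule.
4. **Reporting.** Tabulate, by arm, the sessions received by the date of each week-6 survey. This shows unfinished courses in the immediate arm and any controls who answered after starting. Keep survey dates fixed from baseline in both arms, and do not tie them to session completion.

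The cost is one sentence in each of three sections, one descriptive table, and for some controls a slightly longer wait counted from randomisation. No new survey is needed. The downside is a narrower maintenance claim. For controls who have already started CRAFT, item 3 comes too late, but the other three items still apply.
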